#### Determination of anemia in blood samples

Blood samples will be collected alternately via finger-prick or venous draws to monitor hematocrit levels and anemia in children for the baseline study and clinical trial. Blood for anemia measures will be collected in capillary tubes and spun in a microhematocrit centrifuge. The volume of red blood cells compared to the total blood volume (red blood cells and plasma) will be measured using a manual microhematocrit reader. Anemia will be defined using age-specific WHO thresholds adjusted on the basis of altitude. According to the WHO, children aged 5–11 years who have a hematocrit less than 0.34 and children aged 12–15 years who have a hematocrit less than 0.36, are considered anemic [29].

#### Immune markers in venous blood samples

For the clinical trial, 20 % of enrolled participants will have their venous blood samples separated into plasma, peripheral blood mononuclear cells (PBMCs), and red blood cells by density-gradient centrifugation at each sample collection. A random number generator will be used to equally subsample from the participants in each arm of the study, and the samples from these participants will be processed for PBMCs at each venous blood draw. The plasma will be removed and aliquoted for storage at −20 °C for antibody detection against parasite-specific antigens. PBMCs will be stimulated and cultured at 37 °C for 48 hours for cytokine production. The supernatants will be collected and stored at −20 °C until assayed for cytokine content (e.g., production of interferon gamma (IFNγ), tumor necrosis factor alpha (TNFα), interleukin (IL)-4, IL-13, IL-10, IL-17, IL-22) using bead-based immunoassays. Blood from the remaining children will be centrifuged and separated into plasma and cells upon collection. The plasma will be removed and aliquoted for storage at −20 °C for cytokine detection and for antibody detection against parasite-specific antigens by enzyme-linked immunosorbent assay.

#### Microbiota analyses by 16 s sequencing

DNA extracted from stool samples will be used for high-throughput Illumina sequencing to generate sequence data on the taxonomic composition of the gut microbiota. Sequences will be assigned to operational taxonomic units (OTUs), and the relative abundance of microbial taxa will be calculated using the proportion of OTUs present in each sample. Tests to identify significant differences in the relative abundance of bacterial taxa between groups will be conducted, and *α*-diversity and *β-*diversity measurements will be made. Statistical methods, combining dimension reduction using principal coordinate analysis and regression techniques for correlating microbiota analysis and parasite identification with immune data from blood, will be used to generate a comprehensive portrait of cellular and molecular events in the intestinal tract.

### Endpoints

#### Primary endpoint

The primary endpoint of this study is the total incidence of diarrheal disease, i.e., the total number of diarrheal episodes assessed through weekly active and passive surveillance during the 12-month study period. Diarrhea will be defined according to WHO guidelines, which is three or more loose stools in a 24-hour period or at least one bloody/mucoid stool [34]. To be considered a new episode of diarrhea, at least three intervening days of normal stools without other gastrointestinal symptoms need to have passed between diarrheal occurrences [35].

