The proposed study will be conducted in Vietnam, which has among the highest prevalence levels of human STH of any Western Pacific country [20]. Diarrheal disease also remains a major cause of mortality and morbidity in children in Vietnam, with 11 % of deaths in children aged 0–5 years being due to diarrhea [21]. Recently, the causative agents of diarrheal disease in children under 5 years of age in Ho Chi Minh City, Vietnam, were identified, with Norovirus, Rotavirus, *Campylobacter, Salmonella,* and *Shigella* being the main pathogens isolated from diarrheal patients [22]. Further analysis of a subset of these samples by real-time polymerase chain reaction (PCR) found STH eggs in 6/342 (1.8 %) diarrheal samples, whereas 41/123 (33.3 %) of healthy control samples were positive for STH (our unpublished data). Previous studies have found that real-time PCR is sensitive enough to detect even one STH egg in 200 mg of fecal material [23]. No statistical differences in demographics or personal hygiene between helminth-infected and helminth-uninfected individuals were present, including age, sex, address, household size and income, water and food resources, toilet type, probiotic usage, or hand-washing practice. The significantly higher prevalence of STH infections in healthy controls compared to diarrheal patients suggests that STH may be beneficial to children in combating the pathogens that cause diarrhea. Thus, the primary objective of this study is to investigate the effects of 400 mg albendazole treatment on the incidence of diarrheal disease caused by viral and bacterial pathogens in school children in southern Vietnam. This study will provide new insights into the role of co-infections in the success of treatment strategies and may inform public health policies to mitigate indirect effects of mass deworming programs.

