## Methods/design

### Study aims

We hypothesize that anthelmintic treatment with 400 mg albendazole will lead to an increase in the incidence of diarrheal disease caused by viral or bacterial pathogens, potentially due to alterations to the host immune response and/or gut microbiota with helminth removal. To test this hypothesis, we will compare the incidence of diarrheal disease between individuals receiving anthelmintic and placebo treatment in a randomized, double-blinded, placebo-controlled trial over the course of 12 months. Secondarily, this study will determine the prevalence and intensities of helminth, viral, and bacterial infections in the study location, alterations in host immunity and the gut microbiota with helminth and pathogen clearance, changes in mean *z* scores of body weight indices over time, and the number and severity of adverse events (AE). The study design presented herein aims to investigate whether there are any indirect effects of anthelmintic treatment on non-target diarrheal pathogens, with the goal of informing deworming programs in co-infected populations.

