#### Parasite detection in stool samples

Nucleic acids will be extracted from fecal samples using the MP FastDNA SPIN Kit for Soil, the NucliSENS easyMAG system, and/or the Roche MagNA pure 96 automated nucleic acid extraction machine. The extracted deoxyribonucleic acid (DNA) and ribonucleic acid (RNA) from all collected stool samples will be used as templates for real-time PCR for helminth, bacteria, and virus identification. Samples will be tested for *A. lumbricoides*, *T. trichiura*, *N. americanus*, *A. duodenale*, and *Strongyloides stercoralis* for helminth infection, *Shigella*, *Campylobacter*, and *Salmonella* for bacterial infection, and Rotavirus and Norovirus for viral infections using previously validated primers and probes [31–33]. Fecal samples will also undergo microscopic investigation using the Kato-Katz method for helminth detection and egg quantification during the baseline study. Diarrheal stool samples will be analyzed using the Luminex xTAG Gastrointestinal Pathogen Panel for simultaneous detection and identification of a wide array of intestinal pathogens. Additionally, stool samples will be stored and assayed retrospectively, where required, to detect additional pathogens.

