### Sample size and statistical considerations

In southern Vietnam, approximately 30 % of school-aged children are infected with at least one species of STH [20]. This percentage was supported by our preliminary study of helminth infections in healthy children in Ho Chi Minh City, Vietnam (our unpublished data). Most data on diarrheal incidences due to enteric infections have focused on children under 5 years of age. For the bacterial pathogens, *Shigella*, *Campylobacter*, and *Escherichia coli*, diarrheal rates in this age group range from 3.3 cases/child per year in children under 1 year old to 0.7 cases/child per year in 4-year-olds in Vietnam [36]. Few studies have investigated the incidence of diarrheal events in children over 5 years of age. Considering the diarrheal attack rate in 4-year-olds due to these three pathogens, it is estimated that school children over 5 years of age will have a probability of at least 0.6 of experiencing one or more diarrheal episodes due to any viral or bacterial species during the 12-month follow-up duration. The clinical trial is powered to detect a 15 % absolute increase of this probability (from 0.6 to 0.75) due to anthelmintic treatment in both the subgroups of helminth-infected and helminth-uninfected participants. For 80 % power at the two-sided 5 % significance level, a total of 298 helminth-infected and 298 helminth-uninfected participants will be needed. Of note, this sample size calculation is conservative insofar that the actual study endpoint measures the number of diarrheal episodes and is thus more sensitive than the binary assessment of whether at least one episode occurred or not. To account for potential inadequacies in our assumptions and some loss to follow-up, the sample size was increased by 15 %. Thus, a total sample size of 700 participants: 350 helminth-infected and 350 helminth-uninfected children, will be recruited from the baseline study (using a random number generator to subsample from those groups, as needed) to the clinical trial and will be equally randomized to receive either anthelmintic or placebo treatment. Assuming that approximately 30 % of school-aged children are infected with at least one species of STH infection [20], to enroll 350 helminth-infected children, up to 1800 school children will be enrolled in the baseline study, in order to account for any uncertainties in the helminth prevalence during the baseline study and for decreased participant enrollment for the clinical trial.

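### The objective and hypothesis concern diarrhea caused by viruses or bacteria, but the primary endpoint counts all diarrhea and no pre-specified comparison counts pathogen-positive episodes

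*Protocol article*

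**What the plan says.** **Question.** The Background gives the primary objective as "the effects of 400 mg albendazole treatment on the incidence of diarrheal disease caused by viral and bacterial pathogens". Study aims hypothesizes that albendazole "will lead to an increase in the incidence of diarrheal disease caused by viral or bacterial pathogens".

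**Test of the hypothesis.** The same section then says "we will compare the incidence of diarrheal disease between individuals receiving anthelmintic and placebo treatment", with no restriction by cause. The Primary endpoint section makes this "the total number of diarrheal episodes assessed through weekly active and passive surveillance during the 12-month study period". An episode is defined by stool frequency or by blood or mucus in the stool. Statistical analysis models that count per child by mixed-effects Poisson regression with follow-up time as offset.

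**Secondary endpoints.** Viral and bacterial infections appear as prevalence and intensity at visits, during diarrhea and two weeks after it. Statistical analysis limits the main comparison between arms to stools from scheduled visits and leaves the additional stools to exploratory work.

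**Laboratory.** "Diarrheal stool samples will be analyzed using the Luminex xTAG Gastrointestinal Pathogen Panel for simultaneous detection and identification" of intestinal pathogens. The Clinical trial section has a nurse collect a stool when an episode is reported.

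**Sample size.** The planning probability of at least 0.6 is for "experiencing one or more diarrheal episodes due to any viral or bacterial species during the 12-month follow-up duration". It is extrapolated from a rate of "0.7 cases/child per year in 4-year-olds in Vietnam" for three bacterial pathogens. A rise to 0.75 with 80% power at two-sided 5% is said to need 298 children in each helminth stratum. The calculation is called conservative because the real endpoint is a count rather than yes/no.

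**The concern.** The objective, hypothesis and planning probability share one outcome (viral or bacterial diarrhea). The primary endpoint and its model use another (diarrhea of any cause). All-cause diarrhea may be a reasonable proxy, but the article never calls it one.

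Two things are at stake.

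- **Interpretation.** An all-cause excess on albendazole could not, without more, be attributed to viral or bacterial susceptibility. An all-cause null could reflect a real cause-specific effect diluted by other episodes. The comparison that would separate these, pathogen-positive episodes per child by arm, is not among the listed endpoints.
- **Stated power.** The 80% belongs to a yes/no outcome of viral or bacterial cause. The article acknowledges the step from yes/no to count, but not the step from cause-specific to all-cause.

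**Working it through.** **1. The outcome in each section**

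| Section | Outcome | Cause |
|---|---|---|
| Background, Study aims (hypothesis) | incidence of diarrhea | viral or bacterial |
| Sample size | at least one episode in 12 months (yes/no) | viral or bacterial |
| Primary endpoint, Statistical analysis | number of episodes per child | any |
| Secondary endpoints | prevalence and intensity of infection | viral or bacterial, but not an episode count |

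No row is a count of viral or bacterial episodes per child.

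**2. The plan's own figure**

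Inputs from the sample size section: 0.60 v 0.75, two-sided 5%, 80% power. Unpooled normal formula:

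n per arm = (0.60×0.40 + 0.75×0.25) × (1.960 + 0.842)² / 0.15² = 149.1

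That is 298 per stratum, as stated. The figure is sound for the outcome it was computed for.

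**3. Dilution of the rate ratio**

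With Poisson counts the risks imply yearly rates of −ln(0.40) = 0.916 and −ln(0.25) = 1.386, a rate ratio of 1.51 and a difference of 0.470. Let f be the viral or bacterial share of control episodes. The documents give no value, so f is assumed. Other-cause episodes are taken as equal in both arms.

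- f = 0.7: control 0.916/0.7 = 1.309, treated 1.309 + 0.470 = 1.779, ratio 1.36
- f = 0.5: control 0.916/0.5 = 1.833, treated 1.833 + 0.470 = 2.303, ratio 1.26

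**4. Power of the all-cause count, per stratum (149 per arm)**

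Power = Φ( ln(RR) / √[(1/m₀ + 1/m₁ + 2k)/149] − 1.96 ), where m₀ and m₁ are the all-cause rates and k is the negative binomial dispersion (assumed).

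The rates must be re-solved for each k so that the risks stay at 0.60 and 0.75. From P(no episode) = (1 + k·m)^(−1/k):

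- k = 0.5: 1.162 v 2.000 (ratio 1.72)
- k = 1: 1.5 v 3.0 (ratio 2.0)

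| k | f = 1 | f = 0.7 | f = 0.5 |
|---|---|---|---|
| 0 | 96% | 90% | 80% |
| 0.5 | 99% | 94% | 81% |
| 1 | 99.8% | 97.5% | 87% |

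Holding 0.916 v 1.386 fixed while setting k = 1 gives 74%, 54% and 36%. But at k = 1 those rates mean risks of 0.916/1.916 = 0.48 and 1.386/2.386 = 0.58, a 10-point effect rather than the planned 15 points. Those figures are not power for the protocol's effect.

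**5. The planning risk**

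0.7 per year gives 1 − e^(−0.7) = 0.503, and 0.60 needs 0.916 per year. The gap, 0.916 − 0.7 = 0.216 per year, would have to come from viruses and other bacteria, because the 0.7 covers only *Shigella*, *Campylobacter* and *E. coli*. The article does not quantify this step.

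**The case against.** **All-cause diarrhea is a defensible primary endpoint.** It needs no stool, so it loses no episode for want of a sample and is not affected by incidental detections. Study aims says openly that this comparison tests the hypothesis. This stands: the primary endpoint should stay. A reader might infer that the trial's question goes unanswered, but the documents do not support that. The all-cause comparison is an indirect, possibly diluted test, and infection during diarrhea is recorded.

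**Power.** A reader might infer that the trial is underpowered. The table in step 4 does not support this for f of 0.5 or more, and it is per stratum. The main analysis pools both strata: with 298 per arm, f = 0.5 and k = 0, power is 98%. Dilution also assumes that other-cause episodes are unaffected by treatment. The Background's own rationale includes more *Giardia* and other protozoa after deworming, so they might rise too.

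**Planning risk.** A reader might infer that 0.6 contradicts its cited basis, since 0.7 per year gives 0.503. It does not: three bacteria in 4-year-olds is a narrower outcome than any virus or bacterium. What stands is that 0.6 is an unquantified extrapolation. The cited rates fall with age, from 3.3 under one year to 0.7 at four, and participants are 6–15.

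**Could this be left to an SAP?** Analysis detail could. But the article lists its endpoints and says which stools enter the main comparison, and a per-child count of pathogen-positive episodes is in neither place.

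**Conclusion.** The mismatch is real and visible in the text. The objective, hypothesis and planning probability are cause-specific; the primary endpoint is all-cause; no pre-specified comparison between arms counts pathogen-positive episodes. The trial as written can conclude on diarrhea of any cause. Its viral or bacterial conclusion would rest on indirect or exploratory evidence.

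The numerical size is conditional. The rate ratio falls from 1.51 to 1.36 or 1.26 if 30% or 50% of control episodes are other-cause and unaffected by treatment, with no overdispersion. Both shares are assumptions. Under the planned 0.60 v 0.75 effect, count power per stratum stays at about 80% or more at those shares. At a 60% other-cause share with k = 0 it would be 72%, so the reassurance has a limit.

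This is a low-cost improvement in alignment and pre-specification, not a flaw that invalidates the design or the sample size.

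**What to change.** 1. **Primary endpoint.** Keep it, and name it as diarrhea of any cause in the objective, hypothesis and endpoint text.
2. **New key secondary endpoint.** Add the number of diarrheal episodes per child with at least one viral or bacterial pathogen detected, analysed with the same offset Poisson mixed model. State which test results count as positive and how episodes without stool are handled. Report by arm the share of episodes with stool obtained.
3. **Conclusions.** Reserve any statement about viral or bacterial diarrhea for that endpoint.
4. **Sample size section.** Say that 80% power with 298 per stratum is for a yes/no viral or bacterial outcome, and that the remark about being conservative covers only yes/no versus count. Say that 0.6 is an assumption extrapolated from 0.7 per year for three bacteria in 4-year-olds. Give the all-cause rate ratio over a stated range of other-cause shares.

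**Cost.** Protocol and SAP wording only; stool collection at episodes and the pathogen panel are already planned. The new endpoint has two weaknesses to state: episodes without stool are missing from it, and incidental detections are counted.

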#### Secondary endpoints

The secondary endpoints are:Prevalence and intensity of soil-transmitted helminth infections at 0, 0.5, 3, 6, 6.5, 9, and 12 months, and during and 2 weeks after cases of diarrheaPrevalence and intensity of enteric viral and bacterial infections that cause diarrhea at 0, 3, 6, 9, and 12 months, and during and 2 weeks after cases of diarrheaChanges in fecal microbiota composition at 0, 0.5, 3, 6, 9, and 12 months, and during and 2 weeks after cases of diarrheaChanges in blood cytokine levels (TH1, TH2, TH17, and Treg) at 0, 6, and 12 monthsAntibody isotype responses to helminth and diarrheal antigens at 0, 6, and 12 monthsMean *z* scores (height-for-age, weight-for-age, weight-for-height) at 0 and 12 monthsNumber and severity of adverse events (AE) during the 12-month study period

### Sample size and statistical considerations

In southern Vietnam, approximately 30 % of school-aged children are infected with at least one species of STH [20]. This percentage was supported by our preliminary study of helminth infections in healthy children in Ho Chi Minh City, Vietnam (our unpublished data). Most data on diarrheal incidences due to enteric infections have focused on children under 5 years of age. For the bacterial pathogens, *Shigella*, *Campylobacter*, and *Escherichia coli*, diarrheal rates in this age group range from 3.3 cases/child per year in children under 1 year old to 0.7 cases/child per year in 4-year-olds in Vietnam [36]. Few studies have investigated the incidence of diarrheal events in children over 5 years of age. Considering the diarrheal attack rate in 4-year-olds due to these three pathogens, it is estimated that school children over 5 years of age will have a probability of at least 0.6 of experiencing one or more diarrheal episodes due to any viral or bacterial species during the 12-month follow-up duration. The clinical trial is powered to detect a 15 % absolute increase of this probability (from 0.6 to 0.75) due to anthelmintic treatment in both the subgroups of helminth-infected and helminth-uninfected participants. For 80 % power at the two-sided 5 % significance level, a total of 298 helminth-infected and 298 helminth-uninfected participants will be needed. Of note, this sample size calculation is conservative insofar that the actual study endpoint measures the number of diarrheal episodes and is thus more sensitive than the binary assessment of whether at least one episode occurred or not. To account for potential inadequacies in our assumptions and some loss to follow-up, the sample size was increased by 15 %. Thus, a total sample size of 700 participants: 350 helminth-infected and 350 helminth-uninfected children, will be recruited from the baseline study (using a random number generator to subsample from those groups, as needed) to the clinical trial and will be equally randomized to receive either anthelmintic or placebo treatment. Assuming that approximately 30 % of school-aged children are infected with at least one species of STH infection [20], to enroll 350 helminth-infected children, up to 1800 school children will be enrolled in the baseline study, in order to account for any uncertainties in the helminth prevalence during the baseline study and for decreased participant enrollment for the clinical trial.

### Statistical analysis

The main analysis population includes all randomized participants, and the analysis will be conducted according to the randomized treatment arm following the intention-to-treat principle. Subgroup analyses according to helminth infection status at enrollment (infected versus uninfected) will also be performed for all endpoints.

The primary endpoint, the number of diarrheal episodes per subject, will be compared between the two study arms based on mixed-effects Poisson regression models, with treatment as the main covariate and adjustment for helminth infection status at enrollment (infected versus uninfected). To account for subjects lost to follow-up, the subject’s (log-transformed) follow-up duration will be included as an offset in the Poisson regression model. Moreover, to account for potential heterogeneity (i.e., larger between-participant variability than expected by the Poisson regression model), the participant variable will be included as a random effect in the model. If necessary, a random effect of family or household will also be included to account for non-independence of siblings or other co-inhabitants of a household. In a second step, the effect of the following covariates on diarrheal incidence will be explored: age, sex, body mass index, and household characteristics (e.g., type of water supply). A random effect of individual will be included to account for non-independence of repeated diarrheal episodes for a given individual. Additionally, the effect of helminth infection and helminth infection intensity, as determined from longitudinal stool samples, on diarrheal incidence will be investigated.

For the secondary endpoints, the proportion of participants with STH and enteric viral and bacterial infections, as well as the infection intensities at each time point, will be summarized and visualized as line-plots over time. Formal comparisons between the treatment arms will be based on logistic mixed-effects models for proportions and linear mixed-effects models for (log-transformed) intensities using the same covariates and random effects as for the primary endpoint. The baseline measurements will be included in the analysis, but modeled as not depending on treatment arm. For the main comparison between treatment arms, only stool samples from scheduled visits will be included, as stool samples collected 2 weeks after diarrheal episodes may be unequally distributed between treatment arms. However, these additional stool samples will be included in the exploratory analyses. The effect of additional household and environmental factors present at baseline on helminth, viral, and bacterial infections will also be investigated using the same statistical modeling approach outlined above.

The taxonomic composition of the gut microbiota will be analyzed before and after helminth infection, anthelmintic treatment, and diarrhea and will be compared with individual baseline levels, between the two treatment arms, and between helminth-infected and helminth-uninfected individuals. The mothur pipeline [37] will be used to detect microbial composition and diversity between and within samples based upon the proportion of OTUs in each sample and to apply appropriate corrections for any differences driven by rare taxonomic groups of microbes. Tests, such as the LDA Effect Size (LEfSe) algorithm [38], will be used to identify significant differences in bacterial taxa between the different groups of interest.

Cytokine levels and antibody profiles in response to parasite-specific antigens will be analyzed from longitudinally collected blood samples. Cytokine and antibody data will be log-transformed for all analyses, and linear mixed-effects modeling for analysis will be conducted as outline above. Additionally, changes in height-for-age, weight-for-age, and weight-for-height *z* scores between baseline and 12 months will be compared between the two treatment arms based on linear regression with adjustment for the baseline *z* score. Random effects to account for non-independence of siblings or other co-inhabitants from the same household will be included if necessary. Additionally, the overall number of participants with at least one adverse event (AE) or serious adverse event (SAE), respectively, will be compared between the two study arms using Fisher’s exact test. Descriptive tables will be used to summarize the frequency of all recorded AEs and SAEs by arm.

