### Study area

This study will be conducted in three primary schools in Cu Chi district in Ho Chi Minh City, Vietnam. Cu Chi is a peri-urban district on the northwestern border of Ho Chi Minh City. The climate of Cu Chi district is temperate with two distinct seasons: a rainy season from May to November and a dry season from December to April. Agriculture is the main source of income in the province. In 2010, Cu Chi district had a population of approximately 355,822 people, with a population density of 819 persons/km^2^ [24]. A prior study indicated that hookworm infections are the predominant STH in this area, with most children experiencing low infection intensities [25]. Although parts of Vietnam participate in the national deworming program administered by the WHO, the primary schools involved in this study have not provided deworming medication to their school children since January 2014 due to financial costs of the medication. The schools have no plans to provide anthelmintic medication to school children in the upcoming year.

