### Blinding and randomization

The trial participants, care providers, study investigators, outcome assessors, and data analysts will remain blinded throughout the trial period of 12 months. Treatment allocations will not be disclosed to the enrolled participants or study personnel until the conclusion of the study or in case of emergency. Only the study pharmacist, who is not involved in field or laboratory studies, will be privy to the treatment allocations in order to prepare the treatment packages accordingly. Block randomization using a 1:1 randomization ratio, stratification by helminth-infection status (infected versus uninfected), and variable block sizes of 4 and 6, respectively, will be used to randomize subjects into either the anthelmintic or placebo group. The randomization list will be generated according to OUCRU standard operating procedures. Briefly, a research biostatistician will establish a statistical code to generate the randomization list and transfer it to the study pharmacist. The study pharmacist will change the random seed, i.e., the initialization of the random number generator, in the statistical code in order to blind the research biostatistician and then run the code to prepare the final randomization list for treatment preparation. The randomization list will be password-protected and stored on a secure server to which only the study pharmacist has access. Randomization numbers, which correspond to a study ID number and a sachet of study medication, will be assigned to each enrolled participant in the clinical trial in a strict numerical sequence with individual school identifiers. Randomization numbers will be recorded on each participant’s CRF and used to identify the participant’s corresponding blinded treatment package. A total of four masked sachets containing either anthelmintic or placebo treatment will be prepared for each enrolled participant throughout the clinical trial. All participants will receive albendazole treatment at the conclusion of the study (month 12).

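### The primary Poisson model leaves age to an exploratory step and has no school term, so precision available from baseline data is given up; the comparison stays valid, and the gain at ages 6–15 is an assumption

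*Protocol article*

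**What the plan says.** All references are to the protocol article.

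- **Primary model** (Statistical analysis): episodes per child are compared by mixed-effects Poisson regression "with treatment as the main covariate and adjustment for helminth infection status at enrollment (infected versus uninfected"). There is a log follow-up offset and a participant random effect. A household term is conditional: "If necessary, a random effect of family or household will also be included to account for non-independence of siblings".
- **Age and sex** (same section): "In a second step, the effect of the following covariates on diarrheal incidence will be explored: age, sex, body mass index, and household characteristics".
- **School**: recruitment is from three schools (Study area: "This study will be conducted in three primary schools in Cu Chi district in Ho Chi Minh City, Vietnam"). Randomisation numbers are assigned "in a strict numerical sequence with individual school identifiers" (Blinding and randomization). No school term appears anywhere in the analysis text.
- **Stratification** (Blinding and randomization): "stratification by helminth-infection status (infected versus uninfected), and variable block sizes of 4 and 6, respectively". Helminth status is the only stratifier named.
- **Secondary endpoints** (Statistical analysis): the logistic and linear mixed models reuse the covariates and random effects of the primary model. Changes in z score "will be compared between the two treatment arms based on linear regression with adjustment for the baseline" z score, with no helminth stratum mentioned.
- **Age-specific rates** (Sample size and statistical considerations): 3.3 cases per child-year under 1 year of age, falling to "0.7 cases/child per year in 4-year-olds in Vietnam", for *Shigella*, *Campylobacter* and *E. coli*. The section adds that few studies cover children over 5.

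**The concern.** Age and school are fixed before treatment, already recorded, and plausibly related to diarrhoea. Neither the design nor the primary analysis uses them. Any variation in episode counts that they explain goes into the participant random effect, where it widens the interval for the treatment rate ratio. The second step, as worded, looks at the covariates' own effects; it does not promise an adjusted treatment estimate.

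Precision matters here because the trial is powered separately in the infected and the uninfected stratum. The 15% sample size margin also has to cover both loss to follow-up and wrong assumptions. Because the secondary mixed models take over the primary covariates, the same choice runs through the infection prevalence, infection intensity and immune comparisons.

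**Working it through.** **1. The plan's own figure.** Unpooled two-proportion formula, 0.60 v 0.75, two-sided 5%, 80% power:
n per arm = 7.849 × (0.60×0.40 + 0.75×0.25) / 0.15² = 7.849 × 0.4275 / 0.0225 = 149.1, so 298 per stratum. The stated figure reproduces and does not rely on covariate adjustment.

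**2. Implied means.** Under a Poisson count, the control mean is −ln(0.40) = 0.916 and the treated mean is −ln(0.25) = 1.386, a rate ratio of 1.513. Then 1/0.916 + 1/1.386 = 1.813.

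**3. What the documented gradient says.** Over an assumed 4-year span, ln(3.3/0.7)/4 = 0.388 per year, a fall of about 32% per year. All of it lies below the trial's lower age limit of 6. Carried from 6 to 15 it would leave exp(−0.388×9) = 3% of the rate at age 6, so it cannot simply be extended. The slope at 6–15 has to be assumed.

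**4. Gain from adding age.** Let a rate falling by a fraction p per year give r = (1−p)^age, with whole-year ages equally frequent. Age then contributes dispersion k = mean(r²)/mean(r)² − 1. With residual between-child dispersion d, the share of the variance of the log rate ratio removed by age is approximately

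2k / (1.813 + 2d + 2k).

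Example: p = 10%, ages 6–15, k = 0.090, d = 0.5 gives 0.180 / 2.993 = 6.0%.

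| Fall per year | Ages | k | d = 0 | d = 0.5 | d = 1 |
|---|---|---|---|---|---|
| 5% | 6–11 | 0.0077 | 0.8% | 0.5% | 0.4% |
| 5% | 6–15 | 0.022 | 2.3% | 1.5% | 1.1% |
| 10% | 6–11 | 0.032 | 3.4% | 2.2% | 1.7% |
| 10% | 6–15 | 0.090 | 9.0% | 6.0% | 4.5% |
| 20% | 6–11 | 0.140 | 13% | 9% | 7% |
| 20% | 6–15 | 0.378 | 29% | 21% | 17% |

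The narrower age band is included because recruitment is in primary schools, so the upper ages may be sparse. The slopes, age mixes and d are all assumptions.

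**5. Simulation check.** 1,500 runs per scenario, 350 children in one stratum, d = 0.5, quasi-Poisson fits with and without age, at the design rate ratio:

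- Log slope 0.10 per year, ages 6–15: variance reduced by 5%, power 0.88 to 0.90.
- Log slope 0.10 per year, ages 6–11: variance reduced by 2%, power about 0.90 either way.
- Log slope 0.20 per year, ages 6–15: variance reduced by 17%, power 0.81 to 0.88.

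The formula gives 5.5%, 2.0% and 18% for these cases, so the approximation is adequate.

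**6. School.** With three equal schools and the same formula, d from 0 to 1:

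- Assumed rate ratios 1 : 1.1 : 1.2 (k = 0.0055): 0.3–0.6%.
- 1 : 1.25 : 1.5 (k = 0.027): 1.4–2.9%.
- 1 : 1.5 : 2 (k = 0.074): 3.7–7.6%.

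The document supports none of these over the others.

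**The case against.** The strongest reply is that nothing here is an error. The primary model is pre-specified, adjusts for the only stratification factor, carries an offset and allows for overdispersion. Allocation is by individual child, so leaving out school does not invalidate the test. Chance imbalance in age is already covered by the interval of a randomised comparison. All of this stands.

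It can also be said that an article may leave further adjustment to an analysis plan that is not shown. That would hold for a silent text. Here the article itself names what enters the primary model and places age and sex in an exploratory step. An adjusted sensitivity analysis may exist elsewhere, but the primary model is a stated choice.

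Three stronger readings are tempting and are not supported:

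- **That the plan's own figures show diarrhoea falling steeply with age among participants.** They cover children under 5 and three bacteria, whereas the endpoint is all diarrhoea at 6–15 years. The sample size section applies one probability, at least 0.6, to all school children. Taking some fraction of the under-5 slope remains a guess.
- **That the treatment estimate is biased or the test invalid.** It is neither.
- **That the adverse event comparison is faulty for ignoring the stratum.** An unstratified Fisher's exact test is valid after 1:1 allocation within strata, and subgroup analyses by helminth status are planned for all endpoints.

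**Conclusion.** This is an efficiency point of uncertain size. Adding age would remove about 1–9% of the variance of the log rate ratio if rates fall 5–10% per year (slightly under 1% for a 5% fall over ages 6–11). At 20% per year the figure is about 7–29%. The upper end needs a full, even spread of ages 6–15 and no residual heterogeneity once age is known, which the plan's own participant random effect suggests is not expected. School could add anything from nothing to several per cent; no figure in the document bears on it. The gain therefore runs from negligible to material, and a few degrees of freedom among 700 children is a small price for it. The missing helminth stratum in the z-score regression is a minor inconsistency with the primary model.

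**What to change.** Before unblinding, state that the primary Poisson model contains treatment, helminth status, age (continuous) and school (three-level fixed effect), and optionally sex. Keep BMI and household characteristics in the exploratory second step. With a log link and randomised treatment, the rate ratio keeps its meaning when these covariates are added.

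Because the secondary mixed models reuse the primary covariates, say whether they follow the change. In the logistic models the odds ratio becomes conditional on age and school, and the variance figures above do not carry over to them. For consistency, add helminth stratum to the z-score regression.

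The cost is one or two sentences in the analysis section, and 3 degrees of freedom in the primary model (1 for age, 2 for school), or 4 with sex. Age is established at eligibility and school is identified at randomisation, so no new data are needed.
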